### Patients

#### Inclusion criteria

Participants meeting the following criteria will be included:

Participants of either gender, aged between 18 and 60 years.Participants with psychiatrist-diagnosed depression based on the DSM-5 criteria (10).Participants whose HAMD-17 score is between 17–24.Participants who have not previously taken any type of antidepressant.Participants who are assessed as having a low risk of suicide (i.e., score ≤ 2 in the Hamilton question of suicide).Participants who have not received acupuncture treatment for at least 1 year.Participants who are willing to participate in the trial and sign a written informed consent.

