### Sample size calculation

The non-inferiority hypothesis is based on the results of a previous study (11). HAMD-17, as the primary outcome, decreased by 11.3 points in the premedication group and by 10.2 points in the EA group, with an equal standard deviation of 11.5 points. Following these parameters, the proposed non-inferiority boundary is set at -4 points, with a level one type I statistical error equivalent to 0.025 and a desired statistical power standing at 80%. These calculations are supported by the analytical tools implemented in PASS 15.0. The results were obtained for a required sample size of 81 cases per group, and considering a 20% drop rate, 102 cases need to be included in each group, totaling 204 cases. The formula employed to determine the sample size in this trial was listed as:

$${\text{n}}_{\text{A}}={\text{k}}_{{\text{n}}_{\text{B}}}\;\text{and}\;{\text{n}}_{\text{B}}=\left(1+\frac{1}{\text{k}}\right){\left(\sigma \frac{Z_{1-\alpha }+Z_{1-\beta }}{\mu_{A}-\mu_{B}-\delta }\right)}^{2}$$

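### The stated 80% power does not follow from the sample-size inputs: 81 per group gives about 36% with EA 1.1 points worse, and the SD of 11.5 needs justifying at the same time

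*Protocol article*

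**What the plan says.** The primary outcome is the change in HAMD-17 from baseline to week 12 (Primary outcome), and the aim is to show that EA is not inferior to escitalopram (Hypothesis). The Sample size calculation section takes its planning figures from one earlier trial: "The non-inferiority hypothesis is based on the results of a previous study". There the score "decreased by 11.3 points in the premedication group", whereas the comparison arm fell less, "by 10.2 points in the EA group". Both arms are given the same spread: "with an equal standard deviation of 11.5 points". For the margin, "the proposed non-inferiority boundary is set at -4 points". Alpha is 0.025 and the target power is 80%. The section reports 81 per group, raised to 102 per group (204 in total) for 20% dropout. It prints the standard formula, with the difference in means minus the margin in the denominator.

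Entry is limited by the criterion "Participants whose HAMD-17 score is between 17–24" (Inclusion criteria). The scale is said to run from 0 to 54 (Primary outcome). The article does not say whether 11.5 is an SD of change, and does not compare the earlier trial's patients with its own entry range.

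**The concern.** Two inputs to the same calculation look wrong, and they act in opposite directions.

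The first is the direction of the assumed difference. A smaller fall in HAMD-17 is a worse result, so falls of 10.2 on EA and 11.3 on medication put EA 1.1 points closer to the margin. A sample size of 81 looks too small for an SD of 11.5 and a remaining distance of 2.9 points.

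The second is the SD. Nobody who enters at 17–24 can improve by more than 24 points, so an SD of 11.5 around a mean of 10 or 11 is very wide for this population.

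The trial's ability to reach a conclusion is at stake. If its own planning assumptions were true, a trial of this size would more often than not fail to show non-inferiority even though EA lay inside the margin. Correcting only one of the two inputs would mislead in one direction or the other.

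**Working it through.** **Inputs** (Sample size calculation unless noted): mean fall 11.3 on medication and 10.2 on EA; SD 11.5 in both groups; margin 4; alpha 0.025, taken as one-sided because the printed formula uses Z(1−α); power 80%; 81 evaluable per group; 1:1 allocation (Randomization and blinding); entry at 17–24 (Inclusion criteria).

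**Formula.** With k = 1, n per group = 2 × [SD × (1.960 + 0.842) / d]², where d is the distance from the assumed difference to the margin.

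**Step 1: reproduce the stated 81.**

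| How the difference is entered | d | n per group, normal formula | n per group, t-based | Power at 81, t-based |
|---|---|---|---|---|
| EA 1.1 better: (11.3 − 10.2) + 4 | 5.1 | 80 | 81 | 80% |
| No difference | 4.0 | 130 | 131 | 59% |
| EA 1.1 worse, as stated: (10.2 − 11.3) + 4 | 2.9 | 247 | 248 | 36% |

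For the last row, 2 × (11.5 × 2.802 / 2.9)² = 246.9, so 247. For the first, 2 × (11.5 × 2.802 / 5.1)² = 79.8, so 80, and 81 once the t distribution is used. The stated 81 is therefore matched exactly, but only with the sign of the difference reversed.

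Other readings of alpha do not rescue it. With EA 1.1 worse, a one-sided 0.05 needs 195 per group and a one-sided 0.0125 needs 299. The dropout step is correct: 81 / 0.8 = 101.25, so 102. Even if all 102 per group were evaluable, power with EA 1.1 worse would be about 43–44%.

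**Step 2: how large is 11.5 for this entry range?** A variable confined to [L, 24] with mean m has an SD of at most √[(24 − m)(m − L)].

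| Allowed range of the fall in score | Ceiling, m = 10.2 | Ceiling, m = 11.3 | 11.5 as a share of the ceiling |
|---|---|---|---|
| 0 to 24 (nobody worsens) | 11.86 | 11.98 | 96–97% |
| −7 to 24 (week-12 score may reach 24) | 15.4 | 15.2 | about 75% |
| −37 to 24 (full stated scale) | 25.5 | 24.8 | about 45% |

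The looser ceilings are reached only if every patient sits at one extreme or the other. A milder relaxation changes little. If 5% of patients worsen by the full 7 points and the rest are spread as widely as possible over 0 and 24, then with mean 11.3 the share p at 24 satisfies 24p − 0.35 = 11.3, so p = 0.485. The variance is 0.05 × 49 + 0.485 × 576 − 11.3² ≈ 154, an SD of about 12.4.

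A bound that needs no assumption about worsening: the baseline SD within 17–24 is at most 3.5, so an SD of change of 11.5 forces a week-12 SD of at least 11.5 − 3.5 = 8.0.

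**Step 3: both inputs together.** Power at 81 per group (t-based) and n for 80% power (normal formula), with EA 1.1 worse, d = 2.9. SDs below 11.5 are assumptions; the article gives no alternative.

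| SD | Power at 81 | n per group for 80% |
|---|---|---|
| 11.5 | 36% | 247 |
| 9 | 53% | 152 |
| 8 | 63% | 120 |
| 7 | 75% | 92 |
| 6.5 | 81% | 79 |
| 6 | 86% | 68 |

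Setting n = 81 and solving for the SD gives 2.9 / [2.802 × √(2/81)] ≈ 6.6.

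**The case against.** The strongest defence concerns the SD, and much of it stands.

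- A reader might infer that the entry range contradicts an SD of 11.5. It does not. The value lies below every ceiling in Step 2, including the strictest, and that one requires that no patient worsens, which the article nowhere states.
- A reader might point out that a normal curve with mean 11.3 and SD 11.5 puts about 13% of patients beyond the possible 24 points. That shows individual changes could not be normal with those parameters. It does not make the SD impossible, and a comparison of means at 81 per group does not need normal individual changes.
- A reader might infer that an oversized SD undermines the 80%. Taken alone it does the opposite. It inflates n and is conservative: with the sign as the article evidently entered it, an SD of 8 would need only 39 per group.
- The earlier trial is not at hand, so whether 11.5 was an SD of change cannot be judged here.

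None of this touches Step 1. The shortfall from 80% to 36% comes from the direction of the difference, not from the SD, and uses only figures printed in one section. Nor does conservatism in the SD repair it, because the offset is sufficient only below a value that the article never mentions.

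**Conclusion.** The stated 80% power does not follow from the article's own inputs. With EA 1.1 points worse, SD 11.5, margin 4 and one-sided 0.025, 81 evaluable per group gives about 36% power, and 80% needs about 247 (248 t-based). The figure of 81 results from entering EA's deficit as an advantage. That this is how it arose is inferred from the exact match; that 81 is wrong for the stated inputs is plain arithmetic.

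The SD is a secondary point: implausibly large for a change score in patients entering at 17–24, not impossible, and not justified for this population. The two faults partly cancel. The stated power is true only if the SD is about 6.6 or less.

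It does not follow that the trial needs 247 / 0.8, or 309, per group. That would correct the sign and keep an SD that is probably too large. Nor does it follow that 204 is enough: at an assumed SD of 8, the reversed sign shows 98% power and the correct sign 63%.

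**What to change.** Rework the Sample size calculation paragraph in three steps.

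1. Enter the difference as EA 1.1 points worse, so that the distance to the margin is 2.9. If a different true difference is intended, state it and give its basis.
2. Justify 11.5 for patients entering at 17–24, or replace it with an SD of change, or an ANCOVA residual SD, suited to that range.
3. Restate the power of 81 evaluable per group (204 enrolled) over a range of SDs, as in the last table, and say which SD the trial relies on.

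A blinded pooled SD estimate during the trial, with no between-group comparison, would be a useful check but is optional. The cost is one recalculated paragraph. The downside is that the stated power may become less favourable; whether enrolment then needs to change depends on the SD that can be defended.

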### Randomization and blinding

This study uses a single-blind design, concealing group allocations from participants. Only acupuncturists will be aware of the assignments, but they will not be involved in any other part of the trial, including enrollment, evaluation, and data analysis. To increase blind validity, treatment will be performed in a separate room. Meanwhile, communication about the treatment or efficacy between acupuncturists and participants will be avoided to the maximum extent. At the conclusion of the 12-week intervention, the Bang blinding index will confirm the effectiveness of the blinding technique (12). The placebo drugs supplied by Shanghai Xinyi Huanghe Pharmaceutical Co. Ltd. have an identical appearance to the proprietary form of ESC (Bailote), which is supplied by Sichuan Kelun Pharmaceutical Co. Ltd. All medications are regularly dispensed once a week, with seven tablets per box. Patients can pick up their medication from the dispenser at their own corresponding number on the pre-packaged envelopes. Before the start of the trial, each investigator will receive multiple training sessions on the implementation of the standards of this study and will strictly adhere to the principle of separation of departments.

The study will use a block randomization method with a block size of four, facilitated by SPSS version 24.0 software. Eligible participants will be randomly assigned to either the EA or ESC group in equal proportions. An independent researcher will enclose the treatment allocation codes in sequentially numbered opaque envelopes, and another independent researcher will assign participants to the groups based on the corresponding number on the pre-packaged envelopes and randomization schedule. To confirm the effectiveness of the blinding, the acupuncturist will inquire with all participants whether they received EA or SA treatment at the end of the trial. All participants’ information will remain confidential to the acupuncturist and assessors throughout the trial.

### Intervention

Treatment will last 12 weeks, with 3 sessions per week (usually every other day) for the first 8 weeks, decreasing to 2 per week (usually every two or three days) for the remaining 4 weeks, and the follow-up period will be 6 months. Each participant will be required to wear an eye patch and assume a supine position during each 25-minute session, which will be conducted in a private, tranquil environment. The treatment will be conducted by licensed acupuncturists with at least three years of experience in acupuncture practice. ESC and placebo tablets were identical in appearance and were administered as a morning dose. Participants will record details of the drug dose, duration of dosing, and response to dosing in a case report form (CRF). All drugs in the 7-dose kit will be dispensed once a week at regular intervals by specialized drug dispensers at each center. Patients may receive additional medication once a week if they need it, which will be recorded by the dispenser.

### EA group

Participants in the EA group will receive EA treatment with sterile disposable filiform needles (0.25×25 mm and 0.25×40 mm in size, Asia-med GmbH & Co. KG) and take the placebo drugs for three months. The main acupoints involve Baihui (GV20), Yintang (GV29), Guanyuan (RN4), Qihai (RN6), bilateral Zusanli (ST36), and bilateral Sanyinjiao (SP6). The matching points are Neiguan (PC6), Hegu (LI4), Taichong (LR3), Shenting (DU24), Fengchi (GB20), Shenmen (HT7), Sishencong (EX-HN1), Tianshu (ST25), Taixi (KI3), Xinshu (BL15), Ganshu (BL18), Pishu (BL20), Shenshu (BL23), and Shenmai (BL62). The acupuncturist will select two of the above matching points for each treatment according to the individual patient’s pattern. For the acupoints GV20, GV29, DU24, GB20, and EX-HN1, we used sterile, disposable filiform needles measuring 0.25×25 mm; whereas for the remaining primary acupoints, needles measuring 0.25×40 mm were employed. Following needle insertion, the acupuncturist will use rotating or lifting-thrusting techniques to induce the ‘De qi’ sensation. Three electrode pairs from the electro-stimulator (CMNS6-1, Wuxi Jiajian Medical Device Co., China) will be attached to the needles of GV20 and GV29, and bilateral ST36 and SP6 for 25 minutes, delivering a continuous wave with a frequency of 2 Hz, and the intensity will be set based on the tolerance of each patient. is composed entirely of starch, accounting for 100% of its content. The placebo, which consists entirely of starch (100% of its content), is administered simultaneously with EA. Patients are instructed to take the placebo orally once a day, at a dosage of 10 mg. Based on the individual patient’s response and clinical judgment, the dosage can be adjusted to 20 mg if necessary.

### ESC group

Participants will get SA treatment at the identical acupoints as those used in the EA group. The SA group will be administered using placebo needles (Streitberger Placebo needle, Asia-med GmbH & Co. KG) (13, 14). When the blunt needle tip touches the skin, patients will feel a pricking sensation, although no needle is inserted. An electro-stimulator will then be disposed of adjacent to the patients, and electrodes will be connected to the needles at the same acupoints as the EA group. The acupuncturist will activate the electro-stimulator with all settings at zero during the treatment. Patients will be notified when needles are extracted after 25 minutes of treatment. Dry cotton balls will then be applied to press at the acupoints so that patients can sense the removal of the ‘needles.’ We will use ESC as the participant’s antidepressant. The dose of ESC will be the minimum clinical starting dose of 10 mg once daily for three months. During treatment, patients were allowed to increase the dose (up to 20mg) according to the guidance of a professional psychiatrist.

### Outcome measurement

#### Primary outcome

The primary outcome will be the mean change in HAMD-17 score from baseline to week 12. The HAMD-17 is a questionnaire designed to evaluate the symptoms of individuals diagnosed with depression, which is an observer-rated questionnaire consisting of 17 items (15). The scale uses either a 3-point or 5-point rating system and has demonstrated strong reliability and validity, making it a widely used tool in both research and clinical settings. A higher overall score indicates a higher level of depression, with scores ranging from 0 to 54; scores of 0–6 indicate a normal person without depression; 7–16, likely or suspected to have depression; 17–24, mild to moderate depression; ≥25, severe depression. This outcome data will be collected at baseline, during the treatment phase (at 4, 8, and 12 weeks), and at the 16-, 24-, and 36-week follow-ups.

#### Secondary outcome

The depression recovery rate is the percentage of patients with a HAMD-17 score ≤7 after 12 weeks of treatment. The recovery rate refers to the percentage of individuals who have successfully overcome or managed their symptoms of depression, and will be collected at 12 weeks.The depression remission rate is the percentage of patients between 8 ≤ HAMD-17 ≤ 12 after 12 weeks of treatment. The remission rate refers to the percentage of individuals who have achieved a significant reduction in symptoms of depression, which may involve some residual symptoms but not at levels that would meet the diagnostic criteria for depression. This outcome data will be collected at 12 weeks.The Patient Health Questionnaire-9 (PHQ-9) is an essential self-administered depression screening and diagnostic tool for screening and assessing patients’ depressive status (16–18). It consists of nine items that are easily and effectively used to understand a subject’s depression in the past two weeks. The total scores might be anywhere from 0 (no depression symptoms at all) to 27 (daily occurrence of all symptoms). The higher the total score indicates, the more severe the depression. This outcome data will be collected at baseline, during the treatment phase (at 4, 8, and 12 weeks) and at the 16-, 24-, and 36-week follow-ups.The 36-Item Short Form Health Survey (SF-36) is one of the most widely used quality-of-life assessment scales with good reliability and validity (19). It provides a comprehensive overview of the participants’ quality of life in eight dimensions: physiological functioning, physical functioning, somatic pain, general health status, energy, social functioning, emotional functioning, and mental health. Higher scores represent a better health status. This outcome data will be collected at baseline, and during the treatment phase (at 4, 8, and 12 weeks).The dose and frequency of drugs will be recorded by participants based on actual daily dosing from baseline to the 6-month follow-up period.

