**Methods and analysis:**

This is a multi-site, single-blind, randomized controlled trial with two parallel arms. A total of 204 eligible patients will be randomly allocated to two groups: the EA group (receiving EA treatment with placebo drugs) and the ESC group (receiving escitalopram and sham acupuncture treatment). Treatment will last 12 weeks, with 3 sessions per week for the first 8 weeks, decreasing to 2 per week for the remaining 4 weeks. The primary outcome will be the score of the 17-item Hamilton Depression Rating Scale (HAMD-17), and the secondary outcomes will include depression recovery rate, depression remission rate, Patient Health Questionnaire-9 (PHQ-9), 36-Item Short Form Survey Instrument (SF-36), and the dose and frequency of ESC. The Treatment Emergent Symptom Scale (TESS) will be used to assess all adverse effects. Full details of the statistical analysis plan for the primary and secondary outcomes will be described in this article.

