### Statistical analysis

Analyses will be conducted on the intention-to-treat (ITT) population, which comprises all qualified participants who meet the inclusion criteria, have received the intervention at least once, and have provided at least one outcome assessment. In statistical analysis, any missing primary outcome data will be replaced by the last observed data point, in accordance with the ITT principle. Additionally, a Per-Protocol Set (PPS) analysis will be employed to assess those participants who completed the trial without significant protocol violations. Data analysis for this study will be performed using the statistical software SPSS V.24.0. Descriptive statistical analysis will be used for all demographic and clinical characteristics of subjects, such as sex, age, and weight. We will validate the homogeneity of demographic characteristics and examine the variables between the two groups. The number of patients who change their medication dosage will also be counted, and the variations between the two groups and within each group will be analyzed. If measurement data follows a normal distribution and has homogeneity of variance, the data values will be reported as mean ± standard deviation (MD ± SD). Covariance analysis will be used to compare the data across different groups. If the data does not adhere to the assumed normal distribution, the median values (P25, P75) will be used to characterize it. The Mann-Whitney U nonparametric test will be used to compare between groups. The mean ± standard deviation will be used for the description of the continuous variables. Qualitative data will be expressed in terms of frequency and percentage. The student’s t-test will be utilized for comparing measurement data between two groups from baseline to the 6-month follow-up, while the rank sum test will be used for ranked data, and the χ2 test will be used for analyzing categorical data. A paired t-test was used for comparisons before and after treatment within a group, and an analysis of variance was used for comparisons among different groups. Repeated-measurement analysis of variance was used to compare groups at multiple observation points. A significance level of 2.5% will be used for all statistical analyses, using two-tailed testing. Subgroup analysis will be conducted to examine differences between different genders and across various age brackets.

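### The secondary remission rate counts only HAMD-17 scores of 8 to 12, so it has no fixed direction of benefit and, read alone, can hide or reverse a difference between the arms

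*Protocol article*

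**What the plan says.** The abstract states that "the secondary outcomes will include depression recovery rate, depression remission rate", so the two rates are separate outcomes. The Secondary outcome section defines them on the same scale at the same visit. For recovery: "The depression recovery rate is the percentage of patients with a HAMD-17 score ≤7 after 12 weeks of treatment". For remission: "The depression remission rate is the percentage of patients between 8 ≤ HAMD-17 ≤ 12 after 12 weeks of treatment". It then explains remission as the "percentage of individuals who have achieved a significant reduction in symptoms of depression, which may involve some residual symptoms".

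The Primary outcome section gives the direction of the scale, "A higher overall score indicates a higher level of depression", and a set of severity labels. These call 0 to 6 normal and describe the next band as "7–16, likely or suspected to have depression".

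The Statistical analysis section says that "the χ2 test will be used for analyzing categorical data" and that "A significance level of 2.5% will be used for all statistical analyses, using two-tailed testing". It also lists a rank sum test for ranked data but does not link it to these two outcomes. The article nowhere says that the two bands are added together, analysed as one ordered outcome, or that the remission rate is only descriptive.

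**The concern.** A responder-type rate is useful when more is always better. Here the lower limit of 8 removes the patients who did best. Someone who would have scored 12 and instead scores 5 leaves the remission count. Someone who would have scored 15 and instead scores 10 joins it. Someone who goes from 15 to 5 leaves it unchanged. The net difference between arms therefore depends on where patients sit relative to both limits, and its sign does not say which arm did better.

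The definition also does not fit its own explanation. That text allows residual symptoms but does not require them, so a patient who enters at 17 to 24 and ends at 5 meets the description and is still excluded by the cut-off.

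At stake is the reading of one named secondary outcome. A between-group test on the band could show nothing when one arm is better, or favour the worse arm, and the result would be reported as a remission rate. The primary outcome, mean HAMD-17 change, is not affected.

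**Working it through.** The article states no expected remission rate, so there is no figure to reproduce. The check is how the band behaves as outcomes improve.

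**Inputs from the article.** Bands of 7 or below and 8 to 12 (Secondary outcome); entry range 17 to 24 (Inclusion criteria); planned drops of 11.3 and 10.2 points with SD 11.5, and 102 patients per arm (Sample size calculation).

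**Assumptions.** Week-12 scores are normal with mean m and SD s, with half-point cut-offs. The article gives no SD for week-12 scores, so s runs from 4 to 11.5. The value 11.5 is stated for change, so it serves only as an outer bound. The model ignores the floor at 0, which makes it rough at large s.

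**Formulas.** P(≤7) = Φ((7.5 − m)/s). P(≤12) = Φ((12.5 − m)/s). Band = P(≤12) − P(≤7). The band is symmetric about (7.5 + 12.5)/2 = 10, so under this model it peaks at a mean of 10 and falls on both sides.

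**Step 1: mean lowered from 10 to 6.** At s = 5 and m = 10: Φ(0.5) − Φ(−0.5) = 0.691 − 0.309 = 0.383 (from unrounded values). At m = 6: Φ(1.3) − Φ(0.3) = 0.903 − 0.618 = 0.285.

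| SD | 8 to 12, mean 10 → 6 | ≤7, mean 10 → 6 |
|---|---|---|
| 4 | 46.8% → 30.2% | 26.6% → 64.6% |
| 5 | 38.3% → 28.5% | 30.9% → 61.8% |
| 8 | 24.5% → 21.7% | 37.7% → 57.4% |
| 11.5 | 17.2% → 16.2% | 41.4% → 55.2% |

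At SD 6, means of 14 and 6 give the same band rate, 26.2%.

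**Step 2: the planned difference.** 11.3 − 10.2 = 1.1 points. From an assumed baseline of 20.5, the midpoint of 17 to 24, the means are 20.5 − 11.3 = 9.2 and 20.5 − 10.2 = 10.3, close to the peak. At SD 6:

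- 8 to 12: 32.0% in the better arm, 32.3% in the other (difference −0.3 points).
- ≤7: 38.8% and 32.0% (difference +6.8 points).
- ≤12: 70.9% and 64.3% (difference +6.6 points).

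The result depends on the assumed baseline. From 17 at SD 4 (means 5.7 and 6.8) the better arm is lower, 28.2% against 35.3%. From 24 at SD 4 (means 12.7 and 13.8) the band points the right way, 38.3% against 31.5%.

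**Step 3: can a test favour the worse arm?** Take invented counts with 102 per arm, in the order ≤7, 8 to 12, above 12. Arm A has 61, 20, 21 and arm B has 31, 40, 31. A is ahead at both cut-offs: 61 against 31 at ≤7, and 81 against 71 at ≤12. The band gives 20/102 = 19.6% against 40/102 = 39.2%. The Pearson statistic is 204 × (20×62 − 40×82)² / (60 × 144 × 102 × 102) = 9.44, p = 0.002, in favour of B and below the 2.5% level. This shows only that such a result can occur; the benefit assumed is very large.

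**Step 4: the same check on a cumulative rate.** At SD 6 and means of 14, 12, 10, 8 and 6, P(≤12) is 40.1%, 53.3%, 66.2%, 77.3% and 86.1%. It rises at every step.

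**The case against.** Recovery is defined at the same visit on the same scale, and the two rates add up to the proportion at 12 or below. A reader who takes both together can rebuild the missing quantity and will see recovery rise while the band falls. This stands and limits the harm. It does not remove the problem, because the sum is neither defined nor tested in the article.

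The choice of test is partly inferred. The chi-square test is assigned to categorical data in general and a rank sum test to ranked data, and a fuller plan could apply the latter to the three bands. That also stands. Even so, the article defines each rate as a percentage of its own, and the lower limit of 8 is stated text, not a detail left open.

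Three stronger readings are tempting but not supported:

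- A reader might infer that a key endpoint is compromised. The article lists the rate among several unranked secondary outcomes and attaches no hierarchy or power to it.
- A reader might infer that the comparison will point the wrong way. At the planned 1.1-point difference the band mostly fails to separate the arms, and from a high baseline it points correctly.
- A reader might infer that the severity labels prove the bands wrong, because 8 to 12 lies inside the label for likely or suspected depression. An intermediate state with residual symptoms can sit there, and the label does not change the comparison between arms. The direct mismatch is the score of 7, which is outside the normal range in one section and counted as recovered in the next. That is minor.

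**Conclusion.** The point holds for the definition. A closed band of 8 to 12 that excludes the best outcomes is not monotone in benefit, and this follows from the wording without any model.

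Its size rests on the assumed normal scores, SD and baseline. A 4-point improvement in the mean from 10 to 6 lowers the rate by 16.6 points at SD 4 (46.8 − 30.2) but by only 1.0 point at SD 11.5 (17.2 − 16.2). At the planned difference, midpoint baseline and SD 6, the rate differs by 0.3 points while recovery differs by 6.8. Insensitivity is the likelier consequence there; a reversal is possible but not certain. The matter concerns one unranked secondary outcome, is partly recoverable from its companion, and should be corrected because correction is easy.

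**What to change.** Choose one of two changes:

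- Define the second outcome cumulatively, as the proportion with HAMD-17 of 12 or below at week 12, including patients at 7 or below, and give it a name that fits.
- Treat 7 or below, 8 to 12, and above 12 as one ordered outcome, compared with the rank sum test already among the planned methods or with a proportional-odds model.

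If the 8 to 12 band is kept as well, label it descriptive and show it only beside the recovery rate. Separately, reconcile the Primary outcome and Secondary outcome sections on the score of 7.

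The cost is wording in the outcome definitions and one line in the analysis section. No new data, visits or patients are needed. The change should be made before unblinded data are seen.
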